#### 4.4. Individual Withdrawal Criteria

Subjects must be withdrawn from the study if any of the following occurs:

- At their own request. At any time during the study and without giving reasons, a subject may decline to participate further. The subject will not suffer any disadvantage as a result
- If, in the investigator's opinion, continuation of the study would be harmful to the subject's well-being
- At the specific request of the sponsor and in liaison with the investigator (e.g. obvious non-compliance, safety concerns)
- Pregnancy
- Use of prohibited medication
- Any SAE reported
- CTCAE Grade 3 or higher adverse event
- Any laboratory abnormalities that in the judgment of the investigator, taking into consideration the subject's overall status, prevents the subject from continuing participation in the study.
- Any other medically important AE in the judgement of the investigator

#### 4.5. Study Population

The study population will be comprised of adult male and female healthy volunteers. A maximum of 28 subjects will be enrolled in the 3-part study. All subjects are expected to complete the study. Drop-outs will be replaced.

The investigator must ensure that all subjects being considered for the study meet the eligibility criteria. No additional criteria should be applied by the investigator, in order that the study population will be representative of all eligible subjects.

Subject selection is to be established by checking through all eligibility criteria at screening and baseline. A relevant record (e.g. checklist) of the eligibility criteria must be stored with the source documentation at the study site.

Deviation from **any** entry criterion excludes a subject from enrollment into the study.

No additional exclusions may be applied by the investigator to ensure that the study population will be representative of all eligible subjects.

#### 4.6. Prohibited Concomitant Treatment

Except for medication which may be required to treat adverse events, no medication, or herbal remedies other than study drugs will be allowed from the first dosing until all of the Study Completion evaluations have been conducted.

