#### Cohort B1:

| Sequence | Period 1                                             | Period 2                                           |
|----------|------------------------------------------------------|----------------------------------------------------|
| 1 (n=2)  | Solution 1600mg  QD under fed conditions | Chewing tablet 2000 mg QD under fed conditions     |
| 2 (n=2)  | Chewing tablet 2000 mg QD under fed conditions       | Solution 1600  QD under fed conditions |

 highest dose that was tested to be safe and tolerable in Part A.

Each subject will participate in a 21-day screening period, one treatment period with a wash out period of 1 day and an EOS visit (between Day 6 and 8). The wash-out phase might be increased to 2 days depending on  $T_{1/2}$  in early cohorts. The washout phase will be at least 5 times  $T_{1/2}$  based on the PK results of Part A.

Subjects will remain domiciled in the study site from Day -1 until the Day 4 (24h post dose) until the safety assessments have been completed. Subjects will be allowed to leave the study center on Day 4 (safety signals, if any, are expected to occur within 24h from the drug administration, due to the expected short half-life of niclosamide solution) at the discretion of the Investigator, if there are no prohibitive safety findings. The subjects will be asked to return

[figure not shown]

to the study site for the EOS assessments on Day 6 (+2 days). The EOS evaluation has also to be performed if a subject prematurely terminates the study for any reason.

All baseline safety evaluations results must be available prior to dosing.

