### 3.7. Study Completion

Study completion is defined as the date when the last subject finishes the EOS visit and any assessments have been documented and followed up by the investigator. In case of an early study termination, it will be the date of the decision to terminate the study.

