### 4.2. Inclusion Criteria

Each subject must satisfy all of the following criteria to be enrolled in the study:

1. Healthy male or female subjects
2. Age 18-45 years (inclusive) at the time of informed consent signature
3. Body Mass Index (BMI) between 18.0 and 30 kg/m^2, inclusive at screening.
4. Healthy based on physical examination, medical history, vital signs, clinical laboratory tests, and 12-lead ECG performed at screening. If any of the results are abnormal, the subject may be included only if the investigator judges that the abnormalities or deviations from normal are not clinically significant.
5. A resting heart rate between 50 and 90 beats per minute
6. Men must agree to use condoms (including men who have had vasectomies) even if their partner is pregnant (this is to ensure that the fetus is not exposed to the study drug through vaginal absorption) and to not donate sperm and to not plan to father a child during the study and for 3 months after receiving the last dose of study drug. Male subjects must be counselled by the investigator that they should encourage their female partner to use a highly effective method of contraception consistent with local regulations regarding the use of contraceptive methods for subjects participating in clinical studies (e.g. prescription oral contraceptives, contraceptive injections, intrauterine device [IUD]) in addition to the condom used by the male study subject.
7. A female subject of childbearing potential must either commit to true abstinence from heterosexual contact or agree to use, and be able to comply with effective contraceptive methods with a failure rate < 1 % e.g. use of oral (estrogen and progesterone), injected or implanted hormonal methods of contraception by woman with correct and consistent use or placement of an IUD or intrauterine system (IUS) or other forms of hormonal contraception that have comparable efficacy from the time of signing the ICF and for 3 months after receiving the last dose of study drug. In addition to hormonal contraception method by woman, the male sexual partner should use a barrier method (e.g. condom).
8. Woman are considered post-menopausal and not of childbearing potential if they have had:
  - Female sterilization (have had surgical bilateral oophorectomy with or without hysterectomy), total hysterectomy or tubal ligation at least six weeks before taking

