## 7.5. Contraception

Reproductive toxicity and teratogenicity data are not sufficiently reliable for the investigational drug. As this study enrolls women as well who are considered to be of childbearing potential, all suitable measures must be taken to avoid falling pregnant. Male participants and female participants of childbearing potential must maintain highly effective contraception methods starting from signing of the informed consent form and for at least 3 months after the last dose of study treatment.

Highly effective methods of birth control for female participants and female partners of male participant who are able to become pregnant include the methods below (according to the CTFG Recommendations related to contraception and pregnancy testing in clinical methods with a failure rate of less than 1% per year):

- Total abstinence from heterosexual intercourse (when this is in line with the preferred and usual lifestyle of the subject). Periodic abstinence (e.g. calendar, ovulation, symptothermal, post-ovulation methods) and withdrawal are not acceptable methods of contraception.
- Female sterilization (surgical bilateral oophorectomy with or without hysterectomy), total hysterectomy or tubal ligation at least six weeks before taking investigational drug. In case of oophorectomy alone, only when the reproductive status of the woman has been confirmed by follow up hormone level assessment.
- Male sterilization (at least 6 months prior to drug intake). For female subjects on the study the vasectomized male partner must be the sole partner for that woman.
- Use of oral (estrogen and progesterone), injected or implanted hormonal methods of contraception by woman with correct and consistent use or placement of an IUD or intrauterine system (IUS) or other forms of hormonal contraception that have comparable efficacy (failure rate <1 %), for example hormone vaginal ring or transdermal hormone contraception. In case of use of oral contraception, women should be stable on the same product for a minimum of 3 months before taking investigational drug. In addition to hormonal contraception method by woman, the male sexual partner should use a barrier method (e.g. condom).

Men must avoid sperm donation for up to 90 days after treatment

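### Two subject-level rules are wrong as written: the platelet exclusion is stated per mL, and the medication ban has no exception for the hormonal contraceptives that the protocol accepts

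*Protocol*

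**What the plan says.** **Platelets.** Protocol Section 4.3, exclusion criterion 8, excludes subjects with platelets below 150,000 per mL at screening. No other current section gives a platelet unit or a reference range. Section 4.5 makes every entry criterion binding and forbids the investigator to add exclusions.

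**Medication ban.** Protocol Section 4.6 says that "no medication, or herbal remedies other than study drugs will be allowed from the first dosing until all of the Study Completion evaluations" have been carried out. The one exception is medication needed to treat an adverse event. Section 4.4 lists "Use of prohibited medication" among the events after which a subject must be withdrawn.

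**Contraception.** Inclusion criterion 7 (Section 4.2) accepts, among other methods, "use of oral (estrogen and progesterone), injected or implanted hormonal methods of contraception by woman with correct and consistent use". Section 7.5 extends the hormonal options, "for example hormone vaginal ring or transdermal hormone contraception", and states that men, and women able to conceive, "must maintain highly effective contraception methods starting from signing of the informed consent form and for at least 3 months after the last dose". It also expects women on an oral product to have been stable on it for at least 3 months before dosing. Exclusion criterion 2 bars women of childbearing potential who use no highly effective method.

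**The concern.** A numeric exclusion limit is there to take a decision out of the investigator's hands. If the unit makes the limit unreachable, the number does nothing. A low count judged not clinically significant is then admissible under inclusion criterion 4.

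The contraception rules and the medication ban cannot both be followed to the letter by a woman on a self-administered hormonal method. Staying on the method breaches Section 4.6 and triggers withdrawal under Section 4.4. Stopping it breaches criterion 7 and Section 7.5 unless she moves to another accepted method, such as a non-hormonal IUD or abstinence. Section 7.5 allows abstinence only "when this is in line with the preferred and usual lifestyle of the subject". An investigator who lets her continue relies on an exception that Section 4.6 does not contain. One who applies Section 4.4 withdraws a woman whom Section 4.2 accepted and has to replace her under Section 3.1.1.

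**Working it through.** **Platelet limit**

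Inputs: 150,000 per mL (Section 4.3, criterion 8); 1 mL = 1000 µL; 1 L = 1000 mL. Assumption: per µL was intended, since the protocol gives no other unit.

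- Limit as written: 150,000 / 1000 = 150 per µL. In SI form, 150,000 x 1000 = 150,000,000 per L = 0.15 x 10^9/L.
- Limit as presumably intended: 150,000 per µL = 150,000 x 1000 = 150,000,000 per mL = 150 x 10^9/L.
- Ratio: 150 / 0.15 = 1000.
- Two illustrative counts (chosen for scale, not taken from the protocol): 20,000/µL is 20,000 / 150 = 133 times the written limit, and 100,000/µL is 100,000 / 150 = 667 times the written limit. The criterion as written excludes neither.

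What still applies to a low count is inclusion criterion 4 (healthy on laboratory tests, with abnormal values allowed if judged not clinically significant) and exclusion criteria 3 and 16 (investigator opinion).

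**Medication ban against contraception**

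No formula applies, so the rules are set side by side.

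| Rule | Starts | Ends | Contraceptives |
|---|---|---|---|
| Section 4.6 ban | first dosing | Study Completion evaluations | not exempted |
| Criterion 7 and Section 7.5 | consent | 3 months after last dose | hormonal methods accepted |

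1. Consent precedes dosing, so the contraception period starts first.
2. The EOS visit is Day 6 to 8 in Part B, where the second dose is on Day 3, and Day 10 to 12 in Part C, where the last dose is on Day 7. Both give 3 to 5 days after the last dose (6 - 3 = 3 and 8 - 3 = 5; 10 - 7 = 3 and 12 - 7 = 5). The contraception period runs to 3 months after the last dose, so the ban lies wholly inside it.
3. A pill, ring or patch is used repeatedly during the ban, so continued use breaches Section 4.6 as worded. For an implant, injection or hormonal IUS placed before dosing, the text does not settle whether it counts as medication used during the ban.
4. Women relying on abstinence, a non-hormonal IUD, sterilization or a vasectomized partner are not caught.

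**Reach.** Amendment 2 states that Part A data had already been evaluated, so Parts B and C remain: 4 + 12 = 16 planned subjects. Neither the sex split nor the contraceptive methods are stated, so the number affected is unknown and may be zero.

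**The case against.** The best defence is that both slips resolve themselves on a sensible reading. Criterion 7, exclusion criterion 2 and Section 7.5 are specific rules on contraception, and Section 4.6 is a general ban. A site reading the protocol as a whole would not withdraw a woman for using a method that the protocol accepts. The intended platelet figure is also easy to recognise, and inclusion criterion 4 with exclusion criteria 3 and 16 lets the investigator turn away a volunteer with a worrying count.

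This limits the likely harm, and that part stands. It does not make the text right. Section 4.4 leaves no discretion on prohibited medication. Section 4.5 does not let a site enforce an unwritten limit as if it were criterion 8, so it would have to use one of the judgement-based criteria instead.

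Three stronger inferences are tempting but not supported:

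- **A longer ban.** Section 3.7 says "Study completion is defined as the date when the last subject finishes the EOS visit", and a reader might conclude that each subject's ban lasts until then. Section 4.6, however, refers to evaluations having been conducted. That most naturally means the subject's own EOS assessments, whereas Section 3.7 defines a trial-level date.
- **Actual harm.** A reader might infer that women will be withdrawn or that thrombocytopenic volunteers will be dosed. The documents show only that the wording would require the first and that criterion 8 would not prevent the second.
- **A pharmacokinetic remedy.** One might expect that recording contraceptive use would allow PK to be compared by use. Part B has 4 subjects and Part C has 8 on verum across two doses, with an unknown and possibly nil number of users, so no useful comparison can be expected.

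**Conclusion.** Both rules are wrong as written, at low severity. The platelet exclusion is 1000-fold too low if per µL was meant, and it then excludes no realistic volunteer. That unit is an assumption from ordinary laboratory practice, which the sponsor should confirm. The medication ban, read with the mandatory withdrawal rule, contradicts the protocol's acceptance of hormonal contraception. The conflict is clear for pills, rings and patches and unclear for methods placed before dosing. A site would probably resolve both sensibly. Neither slip touches the sample size or the planned analysis.

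**What to change.** 1. Section 4.3, criterion 8: after confirming the intended unit, change the limit to < 150,000/µL (150 x 10^9/L).
2. Section 4.6: add to the exception *and contraceptives permitted by sections 4.2 and 7.5*. Section 4.4 then needs no change, and Section 5.11 already has concomitant medication recorded.

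The cost is one unit and one clause at the next protocol version, approved under Section 9.3. There is one point to weigh: Section 3.2 chose healthy volunteers partly to avoid drug interactions, and the protocol gives no interaction data for hormonal contraceptives. Sections 4.2 and 7.5 already accept these products, so the clause adds no exposure beyond what they allow.

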#### 4.7. Dietary Restriction and Smoking

- No alcohol for at least 48 hours before dosing until after Study Completion evaluation.

- [figure not shown]
- No cigarettes/use of nicotine products for 48 hours before dosing until after Study Completion evaluation.
  - Intake of xanthine (e.g. caffeine) containing food or beverages must be discontinued 48 hours before dosing. Consumption of such foods and beverages (i.e., coffee, tea, soda, chocolate) is not permitted at any time while the subjects are domiciled. If a deviation occurs, it must be noted in the eCRF. During the out-patient phase of the study caffeinated beverages will be restricted to no more than 4 cups/day.
  - Meals should be provided when all other study procedures scheduled for that time have been completed.

Subjects in Cohort 3 of Part A will receive the oral niclosamide solution under fasted and under fed conditions.

- Under fasted condition, subjects will fast for at least 9 hours prior to administration of study medication and will continue to fast for at least 4 hours thereafter. No breakfast will be provided. No fluid intake apart from the fluid given at the time of drug intake is allowed from 2 hours before until 2 hours after dosing.
- Under fed condition, subjects will receive the standard high-fat breakfast according to the U.S. Food and Drug Administration (*Guidance for Industry: Food-Effect Bioavailability and Fed Bioequivalence Studies*; 2002), following an overnight fast of at least 9 hours. Breakfast should be consumed within 30 minutes and the study drug should be administered within 10 minutes after completing breakfast but no more than 30 minutes from the start of the high fat breakfast. Subjects should consume the entire contents of the meal provided. If this is not possible, the approximate percentage of the consumed food should be documented.

Subjects in Part B and C will receive the oral niclosamide solution under fed conditions.

- Under fed condition, subjects will receive the standard high-fat breakfast according to the U.S. Food and Drug Administration (*Guidance for Industry: Food-Effect Bioavailability and Fed Bioequivalence Studies*; 2002), following an overnight fast of at least 9 hours. Breakfast should be consumed within 30 minutes and the study drug should be administered within 10 minutes after completing breakfast but no more than 30 minutes from the start of the high fat breakfast. Subjects should consume the entire contents of the meal provided. If this is not possible, the approximate percentage of the consumed food should be documented.

## **4.8. Other Restrictions**

No strenuous physical exercise (e.g. weight training, aerobics, football) for 7 days prior to dosing until after study completion evaluation.

# **5. Methods and Assessments**

Time points of assessments are listed in the Schedule of Assessments (Tables 1-3).

## **5.1. Written Informed Consent**

Prior to any study-specific procedure or assessment, written informed consent must be obtained from the study subject.

[figure not shown]

## **5.2. Inclusion/Exclusion criteria**

Each subject must satisfy all the criteria mentioned in sections in- and exclusion criteria to be enrolled in the study.

## **5.3. Demographics and Medical History**

Demographic data include year of birth, age and sex.

Relevant medical history data (including smoking history) includes data until screening visit. If possible, diagnoses and not symptoms will be recorded.

## **5.4. Physical Examination**

A standard physical examination will be done at screening visit. All other examinations during the course of the study can be done by orientation on the baseline findings and actual symptoms.

Information for all physical examinations must be included in the source documentation at the study site, only medically relevant findings are recorded in the eCRF. For examinations at the Screening visit, medically relevant findings are also captured as medical history in the eCRF.

## **5.5. Height and Weight**

Height and weight will be measured to calculate BMI. Weight will be also measured and reported before discharge or relocation.

## **5.6. Urine Pregnancy Test**

Female subjects will provide a urine sample for pregnancy testing. If the urine test is positive, subjects will be excluded from study.

## **5.7. Vital Signs**

Vital signs include heart rate, systolic and diastolic blood pressure, and respiratory rate Vital signs may be recorded at any time, if medically imperative for clarification of clinical signs and symptoms.

## **5.8. Body Temperature**

Body temperature will be measured in the ear.

## **5.9. ECG**

Only pathological and clinically relevant findings in 12-lead ECG determined on predefined study days will be documented on appropriate eCRF-pages. No records of numerical values, such as heart rate, particular times and intervals will be collected.

12-lead ECG may be recorded at any time at discretion of the responsible investigator, if medically imperative for clarification of clinical signs and symptoms. Pathological and clinically relevant findings will be documented as adverse events/serious adverse events.

[figure not shown]

## 5.10. Adverse Events

Adverse events will be interrogated for at each contact between the responsible investigator and the study subject. Furthermore, all pathological and clinically significant findings in physical examinations, vital signs, 12-lead ECGs, clinical chemistry including coagulation parameters, and hematology will be documented as adverse events.

Wherever possible, adverse events will be reported based on CTCAE v5.0.

Adverse events will be reported with subject-ID, start and end date, description, grading, seriousness, relationship, action taken and outcome.

## 5.11. Concomitant Medication

Prior and concomitant medications are recorded at the screening visit and reviewed throughout the entire study until end-of-study visit.

## 5.12. Hematology, Chemistry

### 5.12.1. Hematology, Serology and Urinalysis

Following parameters will be determined on the predefined study days: leukocytes, granulocytes, neutrophils, eosinophils, basophiles, lymphocytes, monocytes, erythrocytes, thrombocytes, hematocrit, hemoglobin.

Serum samples will be taken during screening and are analyzed for hepatitis B surface antigen (HBsAg) or a positive HBV core antigen, as well as Hepatitis C virus antibodies, and HIV antibodies ½ (Screening visit only). A polymerase chain reaction (PCR) test for HCV ribonucleic acid (RNA) will be performed in case the subject has a positive HCV antibody test result. In case of seropositivity for HIV, a second analysis by Western Blot will be performed. Results will be available as source data and will not be recorded within the eCRF. Urine will be analyzed using a dipstick only on screening. In case of positivity in a dipstick test, further appropriate analyses will be performed.

### 5.12.2. Clinical Chemistry

Following parameters will be determined on the predefined study days: sodium, potassium, calcium, magnesium, bicarbonate, glucose, creatinine, urea, bilirubin, AST, ALT, GGT, AP.

